**Fig. 1 Fig1:**
[figure not shown]
Flowchart of the study

The study has received ethical approval from the Medical Research Ethics Committee of the Elisabeth Hospital in Tilburg (NL41169.008.12). The trial registration number is ISRCTN77355880 (http://www.controlled-trials.com/ISRCTN77355880).

### Setting

The organizations for sheltered and supported housing in which this study is conducted provide ‘sheltered housing’ and ‘supported independent living’ services. In sheltered housing facilities, people with SMI live together and receive daily supervision from care professionals. In the case of supported independent living, the client lives independently, alone or with family or friends, and receives a certain amount of care at home. Both sheltered housing and supported independent living services are often provided by the same team of professionals. In that case the home base of the team is a sheltered housing facility, from where the team also provides supported independent living services to clients in the same area. The teams consist of ‘key workers’ and ‘support workers’. Key workers coordinate care around a client and draw up support plans and direct the execution of these plans. Support workers support clients in their daily living and are responsible for the execution of (parts of) the support plan. Furthermore, support workers take care of the living environment in a sheltered housing facility. Generally, key workers and support workers are educated as social workers or nurses. The teams are not responsible for the medical/psychiatric treatment of their clients. Most clients receive treatment from external (multidisciplinary) treatment teams from mental health care organizations.

### Interventions

#### CARe methodology

First the overall aims and corresponding theoretical background of the CARe methodology will be explained. Subsequently we will describe the way the methodology will be provided in practice.

#### Theoretical background

The central aim of the CARe methodology is improving the quality of life of people with a psychological or social vulnerability. The CARe methodology addresses this aim in three ways: (1) realizing the client’s wishes and goals; (2) handling vulnerability and reinforcing strengths; and (3) obtaining access to desired environments and improvement of the quality of the client’s living environment and social networks. The CARe methodology is strongly influenced by the concept of ‘personal recovery’ [17], the ‘presence approach’ [49] and the ‘strengths model’ [28, 44, 45, 50].

#### Personal recovery

One of the major objectives of the CARe methodology is to support clients in their personal recovery. In the CARe methodology, the recovery process consists of three phases: stabilization, reorientation and reintegration. When applying the CARe methodology, the individual recovery process of the client is central. In this respect, five clusters of recovery factors have to be investigated and reinforced. These clusters are: (1) motivation, (2) identity, (3) knowledge and skills, (4) social status and (5) social and material resources [44, 45, 50].

#### ‘Presence approach’

The ‘presence approach’ focuses on the professional’s attitude towards and relationship with the client. The fundamental idea of the presence approach is to create an equal relationship with the professional ‘being there’ for the client without focusing directly on the problems. Important attitudes in the presence approach are patience, unconditional attentiveness and receptivity [49]. When applying the CARe methodology, the presence approach is the central starting point of the way in which a worker builds a relationship with the client.

#### Strengths model

The third influence is the ‘strengths model’ of case management of Rapp [28]. The aim of the strengths model is to focus on the personal qualities, talents, and strengths of a person and his or her environment. The model has six principles: (1) focus on an individual’s strengths rather than pathology and limitations; (2) the case manager-client relationship is primary and essential; (3) interventions are based on clients’ wishes and choices; (4) the community is viewed as a source of possibilities, not as an obstacle; (5) the intervention is preferably offered in the community; and (6) people suffering from SMI can recover and continue to learn, grow and change. When working with the CARe methodology the worker and the client map the strengths of both the client and his/her environment, and use these strengths in achieving the clients goals [45, 50].

#### The CARe methodology in practice

In practice, applying the CARe methodology consists of the following six steps (Fig. 2): (1) building and maintaining a constructive relationship with the client; (2) collecting information and making a ‘strengths assessment’ with the client. The strengths assessment can be used to gain an overview of a client’s former, current and desired situation in the fields of daily life, work, social contacts and leisure; (3) helping the client to formulate his/her wishes, make choices and set goals; (4) helping the client to complete a ‘recovery worksheet, this is a concrete plan with (small) tasks and activities that can be done to achieve the client’s goals and wishes’; (5) helping the client to execute the plan; and (6) after completing the process, to learn, evaluate and adjust [44, 45].

**Fig. 2 Fig2:**
[figure not shown]
The CARe Methodology process

#### Training in the CARe methodology

The teams in the intervention group will receive basic training in the CARe methodology. The aims of this training are to train professionals in the principles of rehabilitative and recovery-supportive care and to support clients’ rehabilitation processes in a methodical way. The training consists of seven meetings, i.e., three full-day theory meetings and four half-day meetings in which the practical skills are learned. Qualified trainers from a specialized training institute conduct these meetings.

After the training program, the professionals continue to be supported in working according to the CARe methodology by means of CARe coaching meetings (once every 4–6 weeks) in which practical cases can be discussed. These coaching meetings are guided by a trained ‘CARe coach’ from the organization concerned, who is not a member of the workers’ teams.

#### Care as usual

The teams in the control group do not receive this training in CARe methodology. The workers in those teams will continue to work according to ‘care as usual’. Care as usual implies working according to the outdated CARe methodology and with a minimal level of model fidelity. Because the CARe Methodology is recently adapted, several distinctive differences exist between the outdated form of the methodology and the form the intervention teams will use. The most important difference between teams in the intervention group and teams in the control group teams will be that the control teams will not work with the ‘strengths assessment’ and the ‘recovery worksheet’, which are seen as the most important instruments of the current CARe Methodology. Besides that they will not be supported by the ‘CARe coaching meetings’. Finally, teams in the control group will be asked not to implement new practices oriented on recovery, rehabilitation or strengths for as long as they are participating in the study.

### Recruitment of teams

Because rehabilitation practices are common in sheltered and supported housing facilities in the Netherlands, it is impossible to include teams that do not work according to any rehabilitation method at all. However, to study the effects of the CARe methodology in a randomized design, teams are needed whose methodology is (1) outdated and (2) not adopted by the workers or inadequately applied. These teams will be selected in three steps. First, we will seek out sheltered housing organizations that possess an intention or interest in training their employees in the CARe methodology. Second, each such organization will be asked to make a selection of possible teams suitable for this study; teams in which (most of) the workers do not have training in CARe methodology, or were trained in an outdated version, and in which the CARe principles are downgraded due to, for example, changes of employees. Teams that are already trained in the current CARe methodology will be excluded from this study. Third, a researcher (NB) will interview the team leaders and make a definitive selection by means of the ‘Quick Scan CARe’, an instrument developed to map the general implementation of the CARe methodology in a team. Only teams with a very low level of implementation will be included in the study and randomly allocated to the intervention or the control group.

#### Team inclusion criteria

Teams of three organizations for sheltered and supported housing facilities in the Netherlands will be included. These teams provide sheltered housing and/or supported independent living services to adults with severe mental health problems. These teams work according to an outdated form of the CARe Methodology. Furthermore, in these teams the (outdated) CARe Methodology is not adopted by the workers or is inadequately applied.

### Recruitment of participants

All clients of the participating teams will be asked to participate in the study. An information meeting will be organized at the location and all clients will receive an information brochure. Subsequently clients will be approached individually by the researcher or via the staff.

The participating clients will be asked to give their informed consent in writing to take part in the data gathering and use of the data for the study. This informed consent will be signed before the start of the first interview. Each participant will be informed about his or her right to withdraw from the study at any time. Because the participating organizations already apply rehabilitation principles and specifically the CARe methodology is already part of the participating organizations no informed consent is needed for the group randomization and the receiving of care according to the CARe methodology.

#### Client inclusion and exclusion criteria

Adult clients (>18) who receive services from a team included in the study participate in the study. Clients with too little knowledge of the Dutch language to fill in the questionnaire and/or clients who are unable to give informed consent or participate in the study due to cognitive impairment or clinical symptoms will be excluded.

### Outcome measures

Outcome measures that suit the aims of the CARe methodology have been chosen. Furthermore, outcome measures have been selected on the basis of usage in comparable national and international research, and on their psychometric properties. Other considerations included were: expected effect sizes, sensitivity and interview duration. Based on these requirements the following outcomes and instruments are selected (see also Table 1):

**Table 1 Tab1:** Outcomes and measure

Topic	Instrument	T0	T1	T2	Rater
Primary outcome measures (client level)					
Recovery	Mental Health Recovery Measure (MHRM)	x	x	x	Client
Societal functioning	Social Functioning Scale (SFS)	x	x	x	Client
Quality of life	Manchester Short Appraisal (MANSA)	x	x	x	Client
Secondary outcomes (client level)					
Empowerment	Dutch Empowerment Scale	x	x	x	Client
Hope	Herth Hope Index (HHI)	x	x	x	Client
Self-efficacy	Mental Health Confidence Scale (MHCS)	x	x	x	Client
Need for care	Camberwell Assessment of Needs (CANSAS)	x	x	x	Client
Additional process and control measures (client level)					
Demographic characteristics	Age, gender, nationality, level of education, marital status, living situation, principal daily pursuit, income	x	x	x	Client
Healthcare utilization	Diagnosis, psychiatric care, day care, contacts with care workers, (psychiatric) hospital admission, other care, psychiatric medication	x	x	x	Staff
Psychiatric symptoms	Brief Symptom Index (BSI)	x	x	x	Client
Recovery promoting relation	Recovery Promoting Relationship Scale (RPRS)	x	x	x	Client
Additional process and control measures (team level)					
Knowledge on recovery	Recovery Knowledge Inventory (RKI)	x	x	x	Staff
Fidelity of Care Methodology	CARe Methodology fidelity audit		x	x	Staff and clients
Quality of care	Quality Indicator for Rehabilitation Care (QUIRC)	x		x	Team leader

#### Primary outcomes

Because the CARe Methodology aims to support clients in their recovery and participation with the overall goal of increasing quality of life, we chose these three outcomes (recovery, social functioning and quality of life) as primary outcomes. All these outcomes will be measured by use of self-report measures.**Recovery** will be measured by the Dutch version of the Mental Health Recovery Measure (MHRM), an instrument developed to assess the recovery process of persons with SMI [19]. The MRHM is a self-report instrument with 30 items. The MHRM is a reliable and valid instrument. The instrument comprises three subscales: ‘self-empowerment’ (*α* = 0.90), ‘learning and new potentials’ (*α* = 0.86) and ‘spirituality’ (*α* = 0.94) [19]. All items are rated using a five-point Likert scale that ranges from ‘strongly disagree’ to ‘strongly agree’.The Social Functioning Scale (SFS) will be used to measure **social functioning**. The scale (*α* = 0.80) consists of 19 items and four checklists on seven domains: social engagement/withdrawal, interpersonal behaviour, pro-social activities, recreation, independence-competence, independence-performance and employment/occupation [51].**Quality of life** will be assessed by the Manchester Short Appraisal (MANSA), an instrument to measure quality of life in people with mental illness. The MANSA (*α* = 0.74) consists of 12 subjective items with a seven-point Likert scale (‘could not be worse’–‘could not be better’). Besides the subjective questions on satisfaction, the MANSA contains four yes/no questions, for example, about the presence of a good friend [52, 53].

#### Secondary outcomes

Besides the primary outcomes, secondary outcomes will be used, aiming to get more insight in the effects of the CARe Methodology. All these outcomes will be measured by use of self-report measures.**Empowerment** is the process of people achieving, or having the feeling that they have, control over their own lives. For the measurement of empowerment the Dutch Empowerment Scale (*α* = 0.93) will be used. This scale consists of 40 items distributed over six domains: professional help (*α* = 0.81), social support (*α* = 0.87), own wisdom (*α* = 0.89), belonging (*α* = 0.74), self-management (*α* = 0.74) and involvement in community (*α* = 0.81). The items are scored on a five-point Likert scale ranging from ‘strongly disagree’ to ‘strongly agree’ [54, 55].**Hope** will be assessed by the Dutch version of the Herth Hope Index (HHI), consisting of 12 four-point Likert scale items ranging from ‘strongly disagree’ to ‘strongly agree’. The Dutch version of the HHI consists of two factors, each of six items: ‘view on life and future’ (*α* = 0.8) and ‘self-confidence and inner strength’ (*α* = 0.69) (overall *α* = 0.84) [56, 57].The Dutch version of the Mental Health Confidence Scale (MHCS) will be used to measure health-related **self-efficacy beliefs** (*α* = 0.93). This scale has 16 items with a six-point Likert scale (‘totally no confidence’–‘full confidence’). The instrument has three subscales: optimism (six items, *α* = 0.87), coping (seven items, *α* = 0.76) and advocacy (three items, *α* = 0.93) [58, 59].**Need for care** will be measured by use of the 27-item client-rated version of the Camberwell Assessment of Needs Short Appraisal Schedule (CANSAS). With this instrument the client can score a health or social need as ‘no need’, ‘fulfilled need’ or ‘unfulfilled need’ [60].

#### Additional and control measures

In a complex research project such as this, there may be numerous external influences. Hence, several additional measures will be used to measure some factors that may modify or explain the possible effects.The following **demographic variables** will be measured: age, gender, marital status, nationality, educational status, employment status, income and living situation. These demographics will be measured by use of a client-rated form developed for the study.**Psychiatric symptoms** will be measured by use of the client-rated Brief Symptom Index (BSI) [61].The client-rated **Recovery Promoting Relationship Scale** (RPRS) (*α* = 0.90) will be used to measure to what extent the client experiences the relationship with his or her key worker as supporting his/her recovery. The scale consists of 24 items with a four-point Likert scale ranging from 1 (strongly disagree) to 4 (strongly agree) and with five indicating not applicable [62].**Worker’s knowledge of recovery** will be measured by use of the staff-rated Recovery Knowledge Inventory (RKI) (*α* = 0.80). The RKI consists of 20 items (scored on a five-point Likert scale ranging from strongly disagree to strongly degree) [62, 63]. Some additional questions will be added to the RKI concerning age, level and type of education and whether the worker received a CARe methodology training. All workers in the participating teams will be asked to fill in the RKI.The key workers of the participating clients will be asked to answer questions regarding the psychiatric **diagnosis** (DSM IV) of the client and the **amount of contact** they have with the client (hours per day and/or week). Besides that*,* there will be questions about the client’s **care consumption** in general and his or her use of work/recreation facilities (hours per week).

#### Model fidelity of the CARe methodology

At T1 and T2, a ‘CARe methodology fidelity audit’ will be performed for all the teams aiming to investigate the extent to which the teams work according to the critical ingredients of the CARe methodology. These critical ingredients are: (1) the presence approach, (2) recovery orientation, (3) strengths orientation, (4) working according to the steps of the CARe methodology, (5) each client has a key worker, and (6) certification, learning (coaching) and implementation. This audit consists of individual interviews with clients, key and support workers, the team leader or manager and a CARe coach. These interviews will be conducted by two auditors: a researcher (NB) and an independent CARe coach. This audit will result in a report with quantitative scores on each critical ingredient of the CARe methodology and a total score. This audit will be performed for teams in the intervention group as well as the teams in the control group so that differences in the model fidelity levels between the two groups can be detected. The results of the audits will be used to investigate to what extent client outcomes can be related to the level of implementation of the CARe methodology and its critical ingredients.

#### Quality of care

To assess the overall quality of care at the team level, the Quality Indicator for Rehabilitation Care (QuIRC) is used. The QuIRC is a European instrument developed to assess quality of care delivered in hospitals and community-based mental health units [64]. The QuIRC comprises 145 questions on service quality and provision (e.g., number of beds, treatments and interventions, training and supervision of staff). The QuIRC provides ratings across seven areas of care: built environment, therapeutic environment, treatment and interventions, self-management and autonomy, social interface; human rights and recovery oriented care [64]. In this way we can investigate to what extent the implementation of the CARe methodology influences the overall quality of care; and relate the areas of care to the outcomes of the other instruments on client level as well as on team level. The QuIRC will be filled in by a researcher (NB) based on face-to-face interviews with the team managers.

### Power calculation/sample size

Sample size was calculated taking into account the design effect (due to group randomization) and the expected effect size. The measures with the highest expected effect size within the duration of the study of 20 months are: empowerment (0.38) and hope (0.50) [26, 43]. Cohen’s d was used as the measure for effect size with *α* = 0.05 and a power of 0.80, based on a two-sided test. The design effect used is estimated to be 1.5 based on an average cluster size of 38 and an intra-cluster correlation (ICC) of 0.013. Based on the effect size of empowerment (0.38; the lowest of the two above mentioned) a sample of 128 clients per condition is needed. When taking into account a reduction of 20 % for loss due to follow up, 160 clients per group will be recruited to achieve the required power. To reach a sufficient amount of clients 16 teams will be included in the study, which together provide services to 890 clients.

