### Statistical analysis

Data will be analysed according to intention-to-treat, meaning that participants will be analysed in the group to which they were allocated by randomization [65]. SPSS 19 will be used for the analysis. Because the study has a cluster randomized design, longitudinal multilevel analysis (linear mixed modeling with random intercepts at both team level and individual level) is the analysis method of choice. First, effectiveness of the CARe Methodology on the three primary outcomes, recovery, social functioning and quality of life, will be evaluated. Subsequently, the effectiveness on four secondary outcomes, hope, empowerment, self-efficacy beliefs and need for care will be evaluated. An alpha correction (i.e., Bonferroni adjustment) will be applied across analysis of the primary measures in order to maintain a family-wise alpha level of 0.05. A separate Bonferroni adjustment will be applied to the set of analysis for the secondary measures to maintain their family-wise alpha level at 0.05. Furthermore, in separate analyses we will assess whether different types of predictors explain the outcomes: (1) client characteristics (age, gender, having a partner, type of housing, diagnosis), (2) symptom severity (BSI), (3) health and day care utilization. Only predictors that influence the prediction of the outcome measures will be added tot the final model. Outcomes will be measured at 10 months and 20 months post-baseline (time will be analyzed as a categorical variable).

To detect significant differences in the baseline characteristics between the intervention group and control group descriptive analysis will be used. When necessary these differences will be taken into account in the analysis. Missing data and drop-outs will be analysed and accounted for by multiple imputation if the assumption of data missing at random (MAR) is not violated [66].

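### The stated 80% power is for a secondary outcome (empowerment) at an uncorrected alpha of 0.05; no power is given for any primary outcome at the Bonferroni level used to test it

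*Protocol article*

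**What the plan says.** The section on primary outcomes is explicit: "we chose these three outcomes (recovery, social functioning and quality of life) as primary outcomes". Table 1 and the section on secondary outcomes place empowerment and hope among the four secondaries.

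The section 'Power calculation/sample size' does not use any of the three primaries. It states "The measures with the highest expected effect size within the duration of the study of 20 months are: empowerment (0.38) and hope (0.50"), and then "Based on the effect size of empowerment (0.38; the lowest of the two above mentioned) a sample of 128 clients per condition is needed". The test is two-sided at alpha 0.05 with power 0.80. On clustering it says "The design effect used is estimated to be 1.5 based on an average cluster size of 38" and "an intra-cluster correlation (ICC) of 0.013". Allowing for 20% loss, 160 clients per group are to be recruited, from 16 teams. No expected effect, detectable difference or power is given for recovery, social functioning or quality of life.

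The section 'Statistical analysis' controls multiplicity within two families. For the primaries, a "Bonferroni adjustment) will be applied across analysis of the primary measures in order to maintain a family-wise alpha level of 0.05". For the others, "A separate Bonferroni adjustment will be applied to the set of analysis for the secondary measures".

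**The concern.** The power paragraph and the analysis paragraph describe different tests. The first takes a secondary outcome at alpha 0.05. The second tests each primary at a third of that level and each secondary at a quarter of it. An alpha of 0.05 is thus the level of none of the seven planned outcome comparisons.

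The choice of outcome adds to this. Empowerment and hope were used because they have the highest expected effects. Read plainly, this makes 0.38 a ceiling for the primaries, although the article puts no number on them.

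A reader will take a stated power of 0.80 to refer to the primary question. If it does not, a non-significant primary result could be given more weight as evidence against an effect than the design supports.

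**Working it through.** **Inputs from the protocol article.** Empowerment d = 0.38; hope d = 0.50; two-sided alpha 0.05; power 0.80; design effect (DE) 1.5, from 1 + (38 − 1) × 0.013 = 1.481; 128 analysed per condition; 16 teams, 8 per arm; three primaries and four secondaries, each family with its own Bonferroni correction.

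**Assumptions added here.** One test per outcome, so alpha is 0.0167 and 0.0125; normal approximation; a comparison at one time point without baseline adjustment. The alternative DE of 1.195 is also an assumption: 128/8 = 16 completers per team gives 1 + 15 × 0.013 = 1.195.

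**Critical values.** z = 1.960 (0.05), 2.394 (0.0167), 2.498 (0.0125); z for 80% power = 0.842.

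**Step 1: the plan's own figure.** n per arm = 2 × ((1.960 + 0.842)/0.38)² = 108.7. Times 1.5 this is 163.1; times 1.481 it is 161.0. The stated 128 is not reproduced. Two readings come close, and the article states neither:
- a one-sided alpha of 0.05: 85.6 × 1.5 = 128.4
- DE 1.195 in place of 1.5: 108.7 × 1.195 = 129.9

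The dropout step does reproduce: 128/0.8 = 160.

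**Step 2: the alpha mismatch alone.** Accept that 128 gives 80% for d = 0.38 at 0.05. The standardised difference is then 1.960 + 0.842 = 2.802.
- Primary at d = 0.38: Φ(2.802 − 2.394) = 65.8%
- Empowerment: Φ(2.802 − 2.498) = 61.9%
- Hope: Φ(2.802 × 0.50/0.38 − 2.498) = 88.3%

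**Step 3: 128 per arm with a given DE.** Power = Φ(d × √(128/(2 × DE)) − z). The root is 6.532 at DE 1.5 and 7.318 at DE 1.195.

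| Test | DE 1.5 | DE 1.195 |
|---|---|---|
| Empowerment, d = 0.38, alpha 0.05 (as in the power paragraph) | 69.9% | 79.4% |
| Primary, d = 0.38, alpha 0.0167 | 53.5% | 65.1% |
| Empowerment, d = 0.38, alpha 0.0125 | 49.4% | 61.1% |
| Hope, d = 0.50, alpha 0.0125 | 77.9% | 87.7% |

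With no clustering at all (DE 1), a primary at d = 0.38 has 74.1%, still below 80%. For illustration only, an assumed primary effect of d = 0.30 gives 33% at DE 1.5 and 42% at DE 1.195.

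**Step 4: detectable difference.** For a primary with 80% power at 0.0167, d = (2.394 + 0.842)/6.532 = 0.495 at DE 1.5, and 3.236/7.318 = 0.442 at DE 1.195.

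**Step 5: separating the two causes.** At DE 1.5, power for d = 0.38 is already 69.9% at alpha 0.05, because 128 is too few for the stated inputs. The corrected alpha takes it from there to 53.5%. Only the second fall belongs to this point; the first is a separate arithmetic discrepancy in the same paragraph.

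**The case against.** The strongest objection is that the calculation above is not the planned analysis. The article plans a longitudinal mixed model, and each primary is measured at baseline, 10 and 20 months. If the baseline value were used as a covariate with an assumed correlation of 0.5, 0.6 or 0.7, the residual SD would shrink by √(1 − r²). A primary at d = 0.38 and alpha 0.0167 would then have 68%, 76% or 86% power at DE 1.5, and 79%, 86% or 93% at DE 1.195. This stands as a limit on what is shown: low power under the final model is not proven. But the article claims no such gain, states no correlation and does not spell out baseline adjustment, so the gain cannot rescue the stated figure.

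Three further cautions also stand:
- A reader might infer that no planned test reaches 80%. The documents do not support that. Hope, with d = 0.50, has about 88% at DE 1.195 or if the stated 80% is accepted. It falls slightly short (77.9%) only at DE 1.5. A t reference with 14 team-level degrees of freedom would lower it to 66–77%, but the article does not specify one.
- A reader might treat smaller primary effects as an established number. They are only implied by the word 'highest'.
- Two follow-up times with categorical time could mean more than one test per outcome. The per-test levels of 0.0167 and 0.0125 assume one.

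It is also fair to say that Bonferroni controls the type I error within each family and that no estimate is biased. The fault lies in what is claimed about power. Nor is this a detail left to an unseen analysis plan: the article prints both the power calculation and the multiplicity rule, and they do not match.

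**Conclusion.** The point holds for the primary outcomes and for empowerment. The only power stated belongs to a secondary outcome at a significance level that the analysis does not use, and no power is given for any primary. In an unadjusted comparison, neither a primary at the implied ceiling of d = 0.38 nor empowerment itself has 80% power.

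The loss that can be charged to the alpha mismatch alone is from 80% to about 66% for a primary and about 62% for empowerment. The lower figures of about 53% and 49% also carry the separate sample size discrepancy and should not be attributed wholly to the choice of outcome and alpha.

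The size rests on one test per outcome, the normal approximation and no baseline adjustment. The mismatch itself rests on none of these.

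**What to change.** Restate the power paragraph for recovery, social functioning and quality of life at two-sided alpha 0.0167. Give either the power at a stated effect or the difference detectable with 80% power and 128 analysed per condition: about d = 0.50 at design effect 1.5, or about 0.44 if 16 completers per team is assumed, both without baseline adjustment.

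Label the empowerment figure as a secondary-outcome calculation and restate it at alpha 0.0125. Mark any primary effect below 0.38 as an assumption. Credit a gain from adjusting for the baseline value or from repeated measures only with the assumed correlation stated. Say how many tests per outcome the Bonferroni divisors count. While the paragraph is open, reconcile 128 with its stated inputs, which call for about 163 per condition.

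The cost is some rewording and a less favourable stated figure. Recruitment, randomisation and data collection are unaffected.

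### The design effect of 1.5 assumes 38 clients per team, but the plan recruits 20 per team, and the 128 per condition does not follow from the stated two-sided inputs

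*Protocol article*

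**What the plan says.** Everything is in one paragraph of the protocol article, under Power calculation/sample size.

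- Error rates: "Cohen’s d was used as the measure for effect size with *α* = 0.05 and a power of 0.80", "based on a two-sided test".
- Effect size: "Based on the effect size of empowerment (0.38; the lowest of the two above mentioned").
- Clustering: a design effect "estimated to be 1.5 based on an average cluster size of 38" and "an intra-cluster correlation (ICC) of 0.013".
- Result: "a sample of 128 clients per condition is needed".
- Recruitment after allowing for 20% loss: "160 clients per group will be recruited to achieve the required power".
- Teams: "16 teams will be included in the study, which together provide services to 890 clients".

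The Study design section says that teams are randomised equally, so 16 teams means 8 per condition. Under Recruitment of participants and the client criteria, all clients are approached, but taking part requires written consent, and clients can be excluded for language, cognitive impairment or symptoms.

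**The concern.** The cluster size in a design effect is the number of clients per team who enter the analysis. The number of teams and the recruitment target fix that number, and it is not 38. The article does not say whether 38 is team size, expected participation or something else.

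This matters because the design effect multiplies the sample size directly. A reader cannot tell which figure to believe, or what power 160 recruited per group delivers. Re-running the calculation to settle this shows a second problem: the required number does not follow from the stated inputs, whichever cluster size is used.

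**Working it through.** **Inputs.** From the sample size paragraph: d = 0.38, two-sided alpha 0.05, power 0.80, ICC 0.013, cluster size 38, design effect 1.5, 128 needed and 160 recruited per condition, 20% loss, 16 teams, 890 clients served. From Study design: equal allocation, so 8 teams per condition.

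**1. Steps that reproduce.**
- Design effect: DE = 1 + (m − 1) × ICC = 1 + 37 × 0.013 = 1.481, rounded to 1.5.
- Loss: 128 / 0.80 = 160.

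**2. Cluster size implied by the plan.**
- Recruited: 2 × 160 = 320; 320 / 16 = 20 per team.
- Analysed: 2 × 128 = 256; 256 / 16 = 16 per team.
- If 38 were right: 16 × 38 = 608 participants, or 320 / 38 = 8.4 teams.
- Served: 890 / 16 = 55.6 per team, before consent and exclusions.

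**3. Required number per condition.** Without clustering, n = 2 × (z for alpha + z for power)² / d².
- Two-sided: 2 × (1.960 + 0.842)² / 0.38² = 108.7.
- One-sided: 2 × (1.645 + 0.842)² / 0.38² = 85.6.

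At the stated design effect of 1.5:
- Two-sided: 108.7 × 1.5 = 163, and 163 / 0.80 = 204 recruited.
- One-sided: 85.6 × 1.5 = 128.4, which matches the printed 128.

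**4. Two-sided need by cluster size, ICC 0.013, normal approximation.**

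| Clients per team | Design effect | Need per condition | Recruited per condition (÷ 0.80) |
|---|---|---|---|
| 16 | 1 + 15 × 0.013 = 1.195 | 108.7 × 1.195 = 130 | about 163 |
| 20 | 1 + 19 × 0.013 = 1.247 | 108.7 × 1.247 = 136 | about 170 |
| 38 | 1.481 | 108.7 × 1.481 = 161 | about 202 |

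The 16 per team row is the one that agrees with the plan, since 8 teams × 16 = 128 analysed per condition. The 20 per team row takes cluster size at recruitment and is the cautious bound.

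**5. Power with 128 analysed per condition, two-sided.** Power ≈ Φ(d × √(128 / (2 × DE)) − 1.960).
- DE 1.5: 0.38 × √(128 / 3.0) = 2.48; Φ(0.52) = 69.9%. With DE 1.481 it is 70.5%.
- DE 1.247: 0.38 × √(128 / 2.494) = 2.72; Φ(0.76) = 77.7%.
- DE 1.195: 0.38 × √(128 / 2.39) = 2.78; Φ(0.82) = 79.4%.
- DE 1.195 with a t reference on 16 − 2 = 14 df: about 73%.

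**6. Why one correction alone misleads.** Changing only the cluster size and keeping the one-sided figure would give 85.6 × 1.195 = 102 per condition, which is too few. Changing only the sidedness would give 163, more than the planned team sizes require.

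**The case against.** The strongest reply is that the figures are unexplained rather than impossible together. All clients are invited, so 160 per group can be read as a minimum, and 38 may be an expected participation of about 68% of those served (608 / 890). If so, the trial would have ample power: about 97% at 304 per condition, with the design effect of 1.481 already counted. This stands as a possibility. The article does not say it, however, and it would replace the mismatch with another one, 608 expected against 320 planned.

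It is also fair that the effect of the cluster size alone is mild and in the safe direction. At 16 to 20 per team, 1.5 overstates the design effect, and the corrected need exceeds 128 by only 2 to 8 clients.

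A reader might infer three stronger things that the article does not support:

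- **That 38 is also contradicted by 56 per team.** The 890 are the clients served, before consent and exclusions. A participating cluster smaller than 56 is to be expected.
- **That high uptake would leave the trial short of power because the design effect rises to 1.71.** The sample would grow too; with all 890 taking part, power is about 99%.
- **That the 38 itself causes a loss of power.** It does not. The shortfall on the stated inputs comes from the one-sided figure.

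Finally, a range of ICC values, an allowance for unequal team sizes and a source for the ICC are things an article may leave to the full protocol. Their absence is not part of this point.

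**Conclusion.** The point holds in two parts. First, the cluster size of 38 behind the design effect does not fit 320 clients in 16 teams and is not explained. Second, the 128 per condition does not follow from the stated two-sided test; about 163 does at a design effect of 1.5.

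The errors pull in opposite directions and nearly cancel. Taken literally, the paragraph delivers about 70% power, not 80%. With the team sizes that the plan implies, the need is about 130 to 136 analysed per condition, and 128 delivers about 78 to 79%, or about 73% at 16 per team on 14 df. The practical shortfall at the planned team sizes is therefore small by the normal approximation, but the paragraph's derivation does not support its claim of 80%.

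These figures assume ICC 0.013 and d = 0.38 as stated, equal team sizes, 20% loss and a comparison at one time point. The 14 df figure further assumes a test that treats the 16 teams as the independent units. That a one-sided alpha produced the 128 is an inference from the match (128.4); the article does not say how it was obtained.

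**What to change.** Recalculate the paragraph as a whole from one set of inputs: 16 teams (8 per condition), the expected number of analysed clients per team, ICC 0.013 and two-sided alpha 0.05. Then restate three figures together: the design effect, the number needed per condition, and the power that 160 recruited per group delivers. Say what 38 refers to, or remove it. If participation of 38 per team is in fact expected, say so and give the resulting total of 608 instead of 320.

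The cost is a short recalculation and a few sentences. It also means stating a power slightly below 80% at the planned recruitment. Keeping the 80% instead would mean recruiting about 163 to 170 per group by the normal approximation, and more if a t reference on 14 df is used. The 890 clients served leave room for that, subject to consent and exclusions.
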